### Statistical methods

Physicians will be analyzed according to their randomly allocated group regardless of adherence to the intervention (intention to treat analysis). If physicians transfer to another unit within the health region, we will still be able to monitor their prescriptions. If the transfer is to a different health region (*i.e.*, not Lisbon) we will contact the physician and ask for the missing prescription data. In both cases, prescription of clopidogrel will be adjusted to the new patient list. If a physician retires or we are unable to retrieve data from a physician who moved to a different region, then we will use the last working month’s prescription.

Both groups will be compared on primary outcomes using generalized mixed-effects models. The ratio of COX-2 inhibitors to the entire NSAID class and the ratio of omeprazole to the entire proton pump inhibitor class and respective 95% confidence intervals will be calculated. Statistical significance will be assumed for a p-value less than 0.025. STATA 12.0 (STATA Corp, TX, USA) will be used to conduct the analysis.

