**Figure 1 F1:**
[figure not shown]
Flow of participants.

Baseline data will be collected from the primary care units (number of family physicians, type of primary care unit, urban versus rural setting, baseline prescription of COX-2 inhibitors, baseline prescription of omeprazole) and from the family physicians (age, gender, number of years of practice after vocational training, currently training residents). Participating physicians will agree to schedule three educational outreach visits, one for each guideline.

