### Allocation to intervention and blinding

Clusters will be enrolled and allocated randomly. To achieve a good balance regarding baseline characteristics that can influence the outcome, the allocation sequence will be determined by minimization [22]. This stratified randomization method will balance the control and intervention groups for number of physicians (4 or 5, 6 or 7, 8 to 12), median baseline prescription of COX-2 inhibitors (above or below the regional median), median baseline prescription of omeprazole (above or below the regional median), proportion of physicians with fewer than 10 years of practice after completing vocational training (above or below 50%), and type of primary care unit (family health unit or personalized care unit). All physicians sending the consent statement before the cluster allocation will be included in the study.

The sequence of intervention visits for each unit will be determined by simple randomization.

Allocation concealment will be ensured by the following procedures: the trial manager (hired and not part of the authors research team) will assign a sequential number to each unit as participation forms are received; only anonymized data about participating units will be sent to the trial statistician (sequential number and minimization variables); data will be sent in two batches, one for each half of all units; the sequence of visits will be determined using the random sequence generator from Random.org (http://www.random.org/sequences/); the statistician will blindly allocate units to each trial arm using minimization and return allocation information to the trial manager.

Due to the nature of the intervention, neither family physicians nor detailers can be blinded. Outcomes are routinely collected by the regional health administration independently of the researchers or the trial and will only be sent to researchers after the intervention has ended. Upon receiving prescription data, the trial manager will generate a random code (using http://www.randomcodegenerator.com) to designate intervention and control units and another code for the order of the visits. Data analysts (the trial statistician plus one of the members of the research team) will receive a file with these codes, ensuring they will be blinded to group and visit sequence allocation until all analyses are completed.

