### Sample size

The research team has obtained pilot data from all physicians of three primary care units. This data was used to estimate within unit variability and the intra-cluster correlation coefficient (ICC). Data was also gathered for all the units in the Regional Health Administration to estimate the mean prescription and standard deviation for the primary outcomes. The mean proportion of omeprazole dispensed was 54.0% of all PPIs (standard deviation, SD, 10.1%) and the ICC was 0.027. The mean proportion of COX-2 inhibitors dispensed was 20.6% of all oral NSAIDs (SD 7.4%), and the ICC was 0.249. The Cochrane review on educational outreach visits found a median adjusted risk difference for improvement in compliance with desired practice of 5.6% (interquartile range 3.0% to 9.0%) and 4.8% specifically for prescribing (interquartile range 3.0% to 6.5%) in previous trials [10]. Therefore, we chose to calculate our sample size assuming the intervention would lead to a 5% absolute difference in compliance with guidelines between intervention and control units.

If we assume a mean cluster size of six physicians per unit, a 1:1 allocation ratio of controls per intervention unit, an alpha type error of 0.025, and a dropout rate of about 15%, then a sample of 110 physicians in each group will allow for 80% power to demonstrate a 5% absolute increase in the proportion omeprazole and a 5% absolute decrease in COX-2 inhibitors. To recruit the necessary number of physicians, 38 primary care units will be required. STATA 12.0 (STATA Corp, TX, USA) and its sampsi and sampclus commands were used to calculate sample size.

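### The stated primary analysis names neither the minimisation factors nor baseline prescribing; fitted as a two-group mixed model it would be conservative for COX-2 and less efficient than the data allow

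*Protocol article*

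**What the plan says.** Under Allocation to intervention and blinding, clusters are allocated so that "the allocation sequence will be determined by minimization". The stated purpose is "To achieve a good balance regarding baseline characteristics that can influence the outcome". The five factors are unit size in three categories, two baseline prescribing factors given as "median baseline prescription of COX-2 inhibitors (above or below the regional median), median baseline prescription of omeprazole (above or below the regional median"), the share of physicians with under ten years of practice, and unit type.

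Under Participants and setting, the baseline data taken from units include "baseline prescription of COX-2 inhibitors, baseline prescription of omeprazole".

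Under Statistical methods, the primary analysis is "Both groups will be compared on primary outcomes using generalized mixed-effects models", and "Statistical significance will be assumed for a p-value less than 0.025". No fixed effect other than group is named, and none is ruled out. Under Sample size, the calculation uses "an alpha type error of 0.025, and a dropout rate of about 15"% and has no covariate term.

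**The concern.** Minimisation makes the arms alike on the chosen factors. If those factors predict the outcome, the treatment estimate varies less from one possible allocation to the next than under simple randomisation. A model that omits the factors does not register this. It counts the balanced variation as residual between-unit noise, so its standard error describes a less precise design than the one used. Intervals are too wide and the test rejects too rarely under the null.

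This matters most for modest effects. The primary question is persistence at 18 months, and the Discussion allows that the effect may fall over time. The review cited under Sample size gives 3.0 points as the lower quartile for prescribing. At that size, a conservative test could turn a real lasting effect into a null result.

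**Working it through.** **1. The planned sample size reproduces, without covariates.** Inputs (Sample size): difference 5 points, two-sided alpha 0.025, power 80%, mean cluster size 6, dropout 15%; COX-2 SD 7.4 and ICC 0.249; omeprazole SD 10.1 and ICC 0.027. Sidedness is not stated, but only the two-sided reading gives 110.

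- Formula: n = 2 × [SD × (2.2414 + 0.8416) / 5]², times 1 + 5 × ICC, divided by 0.85.
- COX-2: 41.6 × 2.245 = 93.5 evaluable, and 93.5 / 0.85 = 110.
- Omeprazole: 77.6 × 1.135 = 88.0 evaluable, giving 104. COX-2 therefore drives the size.

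**2. Share of unit-mean variance due to unit type (R).** Shares by unit type come from Strengths and limitations: COX-2 22.8% against 17.8% (gap 5.0); omeprazole 53.1% against 55.5% (gap 2.4). The fraction p of personalized care units follows from the regional COX-2 mean: (20.6 − 17.8) / 5.0 = 0.56.

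- Variance of a six-physician unit mean: SD² × [ICC + (1 − ICC)/6].
- COX-2: 54.76 × (0.249 + 0.1252) = 20.5. Omeprazole: 102.01 × (0.027 + 0.1622) = 19.3.
- Variance due to unit type: gap² × p × (1 − p).
- COX-2, regional mix: 25 × 0.56 × 0.44 = 6.16, so R = 6.16 / 20.5 = 0.30.
- COX-2, assumed 80:20 mix (the protocol expects family health units may be easier to recruit): 25 × 0.16 = 4.0, so R = 0.195.
- Omeprazole, regional mix: 5.76 × 0.2464 = 1.42, so R = 0.07.

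**3. Effect on standard error and error rate.** With unit type fully balanced but not modelled, the model's SE is too large by 1/√(1 − R), and the actual error rate is 2 × [1 − Φ(2.2414/√(1 − R))].

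| Outcome and mix | R | SE too wide by | Actual error (nominal 0.025) |
|---|---|---|---|
| COX-2, regional mix | 0.30 | 20% | 0.007 |
| COX-2, 80:20 mix | 0.195 | 11% | 0.012 |
| Omeprazole, regional mix | 0.07 | 4% | 0.020 |

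For COX-2 with 19 units per arm of six physicians, the model SE is √(2 × 20.5/19) = 1.47. The true SE is 1.47 × √0.70 = 1.23.

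**4. Power.** For a 3-point COX-2 effect, normal approximation, no dropout, regional mix:

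- Unadjusted: Φ[(3 − 2.2414 × 1.47)/1.23] = Φ(−0.24) = 41%.
- Unit type in the model: Φ(3/1.23 − 2.2414) = Φ(0.20) = 58%.
- With the 80:20 mix the same steps give 41% and 51%.

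For the planned 5 points with 93.5 evaluable physicians per arm, COX-2 power is 84% unadjusted and 93% adjusted at R = 0.30, and about 83% and 88% at R = 0.195. Planned power is not lost.

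**5. Simulation check.** This used 38 units of six physicians, minimisation on all five factors in two batches (assumed biased coin 0.8), a 50:50 unit-type mix, and an assumed baseline-to-18-month correlation from 0 to 0.9. Unit means were analysed, 4,000 null trials per scenario.

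- COX-2, unadjusted, t reference: error 0.0055 to 0.010.
- Omeprazole, unadjusted, t reference: 0.007 to 0.026, at nominal when the correlation is 0.
- Omeprazole, unadjusted, large-sample z reference with maximum-likelihood variance: 0.010 to 0.036, so it can exceed nominal.
- Adjusted for the five factors and baseline, t reference: 0.023 to 0.028 in every scenario.

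**The case against.** The strongest objection is that the article does not describe an unadjusted analysis. It names a class of model and leaves the covariates open, and an unseen analysis plan may list them. A reader might infer that the primary comparison ignores the factors; the text supports only that it does not name them. What remains is that the one analysis stated, followed as written, is a comparison of two groups, and the sample size matches that reading.

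A reader might also infer an error rate far below 0.025 for the primary comparison as a whole. The documents support a marked shortfall for COX-2 only. Omeprazole may be near nominal, and with 38 units a z-based test can offset or reverse the conservatism.

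A reader might infer that the trial is underpowered. It is not: the 80% for 5 points was computed without covariates and is kept. Only extra power is given up, and larger gains than those shown need a baseline correlation that the protocol does not supply.

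Finally, nothing here shows a biased estimate, and for COX-2 the error is in the safe direction. All of this stands, and it limits the point to efficiency.

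**Conclusion.** The point holds as a conditional one. If the primary models contain only group and unit, the COX-2 test is conservative (about 0.007 to 0.012 against 0.025, SE about 11 to 20% too wide) and gives up useful power below 5 points. For omeprazole the effect from unit type alone is small (about 0.020), and the total is unknown.

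The COX-2 result needs no assumed baseline correlation. It does rest on these assumptions:

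- the quoted SD is at physician level, as the sample size uses it, and includes the unit-type difference;
- the ICC from three pilot units is about right;
- unit type is almost fully balanced by the minimisation;
- the recruited mix lies between the regional one and 80:20;
- a linear-scale approximation is adequate for the generalized model.

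This is a worthwhile improvement, not a must-fix validity error.

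**What to change.** Pre-specify in Statistical methods that each primary mixed model has a random intercept for unit and these fixed effects besides group:

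- the same outcome's baseline share as a continuous covariate: the unit value already collected, plus the physician's own value if the claims database supplies it (Participants and setting lists baseline prescribing for units only);
- unit type, size category and experience category;
- the other drug's baseline category.

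All five minimisation factors are then represented. Report the unadjusted model as supportive.

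The cost is a sentence or two, with no new participants and no new unit-level data. The physician-level value would be one further request to the claims database. The statistical price is six unit-level degrees of freedom (one each for baseline share, unit type, experience and the other drug, two for size), leaving about 30 instead of 36 with 38 units. A t reference at two-sided 0.025 moves from 2.34 to 2.36. Since the adjusted error rates above were obtained with a t reference, the reference distribution should be stated as well. The protocol reports that no unit had been randomised, so the change can be made before allocation.

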### Outcomes

#### Primary and secondary outcomes

There are two primary outcomes, measured at the physician’s level. One is the proportion of COX-2 inhibitors (anatomical therapeutic classification [ATC] M01AH) prescribed within the entire NSAID class (ATC M01A) in defined daily doses 18 months after the intervention. The other is the proportion of omeprazole (ATC A02BC01) within the entire proton pump inhibitors class (ATC A02BC) in defined daily doses 18 months after the intervention.

There are seven secondary outcomes, also measured at the physician’s level: the proportion of COX-2 inhibitors within the NSAID class at one and six months; the proportion of omeprazole within the proton pump inhibitors class at one and six months; and the number of defined daily doses of clopidogrel prescribed per 1,000 registered patients at 1, 6 and 18 months. The proportion of clopidogrel (ATC B01AC04) within the platelet aggregation inhibitors (ATC B01AC) was not selected as an outcome because the most commonly used drug in that class is acetylsalicylic acid (ATC B01AC06). This drug is generally sold over the counter, and no reliable data of its consumption exists.

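### The 95% confidence intervals planned for the two primary outcomes do not match the two-sided 0.025 test used to judge them

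*Protocol article*

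**What the plan says.** The protocol article names two primary outcomes under Primary and secondary outcomes: "There are two primary outcomes, measured at the physician’s level". They are the COX-2 share of NSAIDs and the omeprazole share of proton pump inhibitors, both at 18 months.

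Under Sample size, the calculation uses "an alpha type error of 0.025" with 80% power and is made "assuming the intervention would lead to a 5% absolute difference in compliance with guidelines" between the arms.

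Under Statistical methods, three statements follow one another:

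- The comparison: "Both groups will be compared on primary outcomes using generalized mixed-effects models".
- The two class shares with their interval level, and directly after it the decision rule: "respective 95% confidence intervals will be calculated. Statistical significance will be assumed for a p-value less than 0.025".

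Nowhere does the article give a reason for 0.025, say whether it is one- or two-sided, or mention a 97.5% interval.

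**The concern.** A 95% interval for a difference corresponds to a two-sided test at 0.05. If the primary test is two-sided at 0.025, interval and test can give opposite messages about the same estimate: the interval excludes no difference while the p-value misses its threshold. A report would then have to call an effect not significant beside an interval that most readers would take as evidence of an effect. The protocol states both levels, so this is not a detail left open for an analysis plan.

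The two levels would agree if 0.025 were one-sided. The first step is therefore to find out which reading the protocol's own sample size supports.

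**Working it through.** **Inputs, all from Sample size.** Difference 5 points; power 80%; alpha 0.025; mean cluster size 6; dropout 15%; COX-2 SD 7.4 and ICC 0.249; omeprazole SD 10.1 and ICC 0.027; stated result 110 physicians per group and 38 units.

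**Step 1: reproduce the stated sample size.** Physicians per group = 2 × [SD × (z_alpha + z_power) / 5]² × [1 + (6 − 1) × ICC] / (1 − 0.15), with z_power = 0.842.

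| Outcome | Alpha 0.025 read as | z_alpha | Before clustering | Design effect | Per group |
|---|---|---|---|---|---|
| COX-2 | two-sided | 2.241 | 41.64 | 2.245 | 109.98 |
| COX-2 | one-sided | 1.960 | 34.38 | 2.245 | 90.8 |
| Omeprazole | two-sided | 2.241 | 77.57 | 1.135 | 103.6 |
| Omeprazole | one-sided | 1.960 | 64.05 | 1.135 | 85.5 |

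COX-2 drives the size. Two-sided 0.025 gives the stated 110 (111 if 41.64 is first rounded up to 42). One-sided 0.025 gives 91 to 93, depending on rounding. Then 110 / 6 rounds up to 19 units per arm, 38 in total, as stated. The trial was therefore sized for a two-sided 0.025 test on each outcome.

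**Step 2: the interval that matches the test.** Two-sided 0.025 corresponds to a 97.5% interval, with multiplier 2.241 against 1.960 for 95%. The ratio 2.241 / 1.960 = 1.144, so the 97.5% interval is 14.4% wider. Equivalently, 1.960 / 2.241 = 0.874, so the 95% interval is 12.6% narrower.

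**Step 3: half-widths at the planned size.** After dropout, 110 × 0.85 = 93.5 physicians per group. SE of the between-arm difference = SD × √(2 × design effect / 93.5).

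- COX-2: 7.4 × √(2 × 2.245 / 93.5) = 1.622 points. Half-width 3.18 at 95%, 3.63 at 97.5%.
- Omeprazole: 10.1 × √(2 × 1.135 / 93.5) = 1.574 points. Half-width 3.08 at 95%, 3.53 at 97.5%.

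An observed difference of 3.18 to 3.63 points (COX-2) or 3.08 to 3.53 points (omeprazole) would give conflicting statements. For example, z = 2.1 gives p = 0.036: not significant by the rule, yet the 95% interval excludes zero.

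**Step 4: how often this would happen.** The chance that p lies between 0.025 and 0.05 equals the power at 0.05 minus the power at 0.025.

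| True effect | COX-2 | Omeprazole |
|---|---|---|
| None | 2.5% | 2.5% |
| 5 points (design) | 86.9% − 80.0% = 6.9% | 88.8% − 82.5% = 6.3% |
| 3 points (assumed) | 10.9% | 11.0% |

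Three points is the lower quartile of earlier prescribing effects cited under Sample size. It is used here only for illustration.

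**The case against.** The strongest reply is that nothing is wrong with the test. The rule of p below 0.025 is explicit, the sample size uses the same level, and the interval is nowhere made a decision criterion. Conventional 95% intervals beside a stricter p-value threshold can be a deliberate choice for estimation, and a reader can rescale them approximately by 2.24 / 1.96. This stands as far as validity is concerned and limits the point to reporting. It does not remove the mismatch, because the article never says that the intervals are descriptive.

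Three stronger readings are tempting, and the document does not support them.

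- **That the intervals are for the wrong quantity.** The wording attaches them to "The ratio of COX-2 inhibitors to the entire NSAID class and the ratio of omeprazole to the entire proton pump inhibitor class", which taken literally are shares and not a contrast. But the sentence before it plans a model-based comparison of the groups, and the exact effect measure may be left to an analysis plan that is not shown. The conflict described here also arises only for an interval around the between-arm difference: an interval around a share near 20% or 54% has no null value at zero.
- **That joint 95% coverage is lost.** Two separate 95% intervals jointly cover about 90% if independent (0.95² = 0.9025), but the protocol never claims joint coverage. It is a normal property of marginal intervals.
- **That the family-wise error is inflated.** It would reach 0.0975 if the outcomes are independent (at most 0.10), but only if the intervals were used as the test, which the protocol does not say.

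**Conclusion.** The stated interval level does not match the stated test. The one-sided reading that would reconcile them is ruled out by the protocol's own 110 per group. The mismatch is one of level (95% where 97.5% corresponds), and its practical effect is a band about 0.45 points wide for each outcome in which interval and decision disagree.

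The point is minor. Type I error, power and sample size of the primary tests are intact; what suffers is the clarity of a borderline result.

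The half-widths, and the frequencies other than the null one, rest on the planned SDs, ICCs, mean cluster size and dropout, a normal approximation, and no precision gain from covariates. The mismatch itself and the 2.5% under the null do not depend on those planning values or on the scale of the effect measure.

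**What to change.** Amend the sentence in Statistical methods to state that 0.025 is a two-sided level for each primary outcome, and that the model-based between-arm difference for each will be reported with a 97.5% confidence interval. If 95% intervals are also shown, label them as descriptive and not used for the decision.

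The cost is one sentence and primary intervals that are 14.4% wider. The decision rule and sample size do not change. Trial status reports that no unit had been randomised when the article was submitted, so at that stage the clarification could be made before any outcome data existed.

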### Data monitoring

Given the nature of the intervention, which poses minimal risks to patients, no data monitoring committee will be established.

### Ethical approval

This protocol has been approved by the ethics committee of the Regional Health Administration of Lisbon and Tagus Valley. Family physicians invited to participate will receive written information about the main aspects of the trial, namely which data are being collected and the procedures to ensure the non-identifiability of individual prescriber data. They will sign a written consent for researchers to access their data. The trial will only collect aggregated and non-identifiable patient data. As such, the ethics committee waived patient informed consent.

### Trial status

At the time of protocol submission, we have obtained ethical approval and have started to contact eligible primary care units. No primary care unit has been randomized.

The trial has been registered in ClinicalTrials.gov (NCT01984034) and ENCePP.eu (http://www.encepp.eu/encepp/viewResource.htm?id=5150).

## Discussion

### Strengths and limitations

Our pilot data about prescription of NSAIDs, acid-suppressive therapy, and antiplatelet therapy suggests that there is room for improving physicians’ prescribing, aligning it with evidence, and potentially leading both to improvements in patient outcomes and cost savings to the Portuguese National Health Service. This paper describes a protocol for a cluster-randomized trial to assess whether educational outreach visits have a long-term (18 months) effect on physician prescriptions. Randomized trials are the gold standard to assess intervention effects, and cluster-randomized trials are an appropriate design when the intervention is an education intervention targeted at healthcare providers [27].

In this trial, it will be impossible to blind physicians and detailers to the intervention. Lack of blinding is expected to overestimate the intervention effects [28,29]. To minimize the effect of this bias, we are using prescription, which is an objective outcome measured independently from the researchers. This outcome also minimizes attrition, since it is possible to continue to assess the prescription behavior even if a physician changes workplace (within the same region).

We have chosen prescription-related outcomes over clinical outcomes. In Portugal, hospital discharge diagnoses (coded through the 9^th^ revision of the International Classification of Diseases) are routinely collected for hospital reimbursement purposes, but are only available after considerable delay. Primary care diagnoses (coded through the 2^nd^ edition of the International Classification of Primary Care) began to be collected in 2007 and are available in the regional database within only one month of registration in the medical record. However, both hospital and primary care diagnoses have not been validated for comprehensiveness and accuracy. Moreover, diagnoses associated with incentives may be recorded more often than those without incentives [30,31]. Hence, we have chosen to use prescription patterns as main outcomes. All prescription data in the National Health Service is gathered by the Ministry of Health for pharmacy reimbursement purposes. Data are available for both ordered and dispensed prescriptions. Pilot data from three primary care units showed that only about 60% of the prescribed drugs are actually dispensed. This likely arises from several factors: lack of patient adherence to prescriptions, the inability of physicians to match monthly amounts of different medicines in the same prescription sheet (hence the patient will not fill the entire prescription), and errors in printing and composing prescriptions that are subsequently not handed to the patient nor removed from the electronic medical record. For all these reasons, we opted to use dispensed prescriptions data as primary outcomes rather than ordered prescriptions.

Proton pump inhibitors and antiplatelets may be placed in chronic prescriptions, valid for up to six months. This means that data for these drugs may include prescriptions as old as six months prior to dispensing (and hence up to six months prior to the intervention). This may result in an underestimation of the intervention’s effect in secondary outcomes (one and six months, which may still include many lingering old prescriptions). This underestimation will be resolved for the primary outcomes (18 months) because by that time all prescriptions issued prior to the intervention will have been dispensed. However, if the intervention effect decreases over time, prescriptions issued as early as 12 months after the intervention may still be dispensed at 18 months and thus lead to an overestimation of the primary outcomes.

The intervention’s effect on physicians may change over time. As the program moves forward, detailers are expected to build a relationship with visited physicians. This may improve the detailer’s ability to change the physician’s prescribing behavior. On the other hand, the physician’s curiosity and willingness to participate may decrease, making him or her less receptive to the intervention. To avoid confounding resulting from the order by which each guideline is presented, we will randomly assign the guideline order for each unit.

We are recruiting family physicians from the three types of primary care units described in the introduction. Preliminary data at the regional level suggests that prescription patterns have greater room for improvement in ‘personalized care units’ (COX-2 inhibitors market share within NSAIDs is 22.8% in personalized care units vs. 17.8% in family health units; and omeprazole market share within PPIs is 53.1% in personalized care units vs. 55.5% in family health units). However, it is possible that recruitment is stronger in type A and type B ‘family care units’, since their contracts with the Regional Health Administrations state incentives for participation in research projects and lower drug expenditure. This differential participation may compromise the generalizability of our findings to the Portuguese NHS, especially if physicians respond differently to educational outreach according to the type of unit in which they practice.

